11.2 Criteria for Discontinuation

The investigator will discontinue the research on the research subject in the event that any of the discontinuation criteria are met.

Discontinuation Criteria

(1) When the research subject wishes to discontinue participation in the research or withdraws consent.

(ii) In case of poor compliance in wearing the study spectacles (e.g., wearing the study spectacles for a significantly short period of time before going to bed 3 hours before bedtime)

(iii) Other cases in which the physician deems it difficult for the subject to continue the research. 12.

12. evaluation items

12.1. Main endpoints

Evaluation of salivary melatonin concentration 12.2.

12.2. Secondary endpoints

Assessment of circadian rhythm

2. evaluation of sleepiness, mood, and motivation (modified version of the NRS scale for sleep)

3. evaluation of sleep quality and quantity (Children's Sleep Questionnaire for Elementary School Children/Chronotype Assessment)

Other exploratory evaluation of effects on sleep, etc. 13.

Safety evaluation

This study will not use test instruments for the purpose of treatment, etc., but will ask research subjects to submit saliva for salivary melatonin testing. In addition, medical treatment based on the results of the questionnaire and medical treatment such as ophthalmoscopy during the preparation of the test apparatus will not be performed. In addition, the study will not assess adverse events, as the tests and questionnaires are not invasive to the research subjects, although they may be restrained. An inquiry desk will be set up for emergency inquiries from research subjects and for health-related consultations.

Statistics

14.1. primary endpoint

In the main analysis, time trends of salivary melatonin concentration (4 time points at 0, 1, 2, and 3 hours, starting 3 hours before sleep onset) were tested by repeated two-way ANOVA for Siamese eyeglass wear and blue light cut eyeglass wear (eyeglass type), and the results showed that salivary melatonin concentration was significantly higher for eyeglass type, time trend and interaction ( 14.2. Secondary Assessment Items

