Based on these findings, we believe that the disruption of children's circadian rhythms due to exposure to blue light at night from the use of smartphones and tablets may cause children to shift their lives to a nighttime pattern, preventing them from getting proper sleep, and contribute to the risk of developing mental and physical disorders in children, which have been on the increase in recent years. In this study, melatonin concentration, which is directly involved in circadian rhythm,7) will be used as an indicator of the effect on circadian rhythm, and a sham-controlled comparative study will be conducted to examine whether the use of glasses that block blue light increases melatonin concentration before and after bedtime and has a positive effect on sleep and diurnal rhythm. As a secondary evaluation, sleep and wake time will be measured with an actigraph, and sleep-related quality of life will be quantified through a questionnaire for study subjects to evaluate the effects of blue light cutoff on sleep quality, diurnal rhythm, daytime concentration, and mood.

If the effects of blue light on children's circadian rhythm and sleep quality are clarified through this study, it is expected to help in the treatment of mental and physical disorders and disorders, including ADHD, in children, which have been increasing in recent years.

6. objective

To examine whether wearing blue light-cut glasses before and after bedtime increases melatonin levels in school children who are habitually exposed to blue light before bedtime, and whether this has a positive effect on their sleep and diurnal rhythm.

7. study design

Prospective, randomized, sham-controlled, single-blind, crossover, exploratory study

8. study subjects and target number of subjects

School children with a habit of exposure to blue light before bedtime, 40 cases

9. study period

Research period: From the date of approval by the Ethical Review Committee to September 2022

Period of case enrollment: Ethics Review Committee approval date - June 2022

10. research methods

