10.1.5 Enrollment and Assignment

Study subjects will be randomly assigned to the "blue light cut glasses pre-fit group" and the "Siamese glasses pre-fit group" in a ratio of 1:1. Assignment will be made at the time of registration in the Web Registration Assignment System. Although the first pair of spectacles to be worn will be specified, the results of the individual allocation for each subject will not be communicated.

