10.1.6. Survey Methods and Items

The study will be conducted in the home of the research subjects under the supervision of their custodians. Among the potential research subjects who have applied to the recruiting company, the study will be conducted on those research subjects who have given written explanation of the study to the potential research subjects, obtained written consent and assent, and meet the eligibility criteria.

During the study, the study subjects will be instructed to lead a normal life, but to disable the blue light cut mode (night mode, night mode, etc.) on the LED display electronic terminal in consideration of its impact on the study results.

The first wearing of the test spectacles will be on the 1st day and will be completed on the 14th day. The first day of wearing the test spectacles shall be Day 1 and shall be completed on Day 14, and the switching of the spectacles shall be started on Day 22 and completed on Day 35. The first day of the test (Day 1 and Day 22) should be a Friday. In addition, an optional short wearing practice session may be conducted on the day prior to Day 1.

From Day 1 to Day 14 of the prior wearing period, the blue light cut glasses prior wearing group will wear blue light cut glasses and the Siamese glasses prior wearing group will wear Siamese glasses for approximately 3 hours before bedtime every day (14 days of wearing period). Days 15 to 21 will be a non-wearing period for each group, during which the subjects will wear their regular eyeglasses. From Day 22 to Day 35 of the switching period, the subjects in the blue light-cut glasses-first group will wear Siamese glasses, and those in the Siamese glasses-first group will wear blue light-cut glasses for approximately 3 hours before bedtime every day (for 14 days). The test spectacles will be made with the same power as the spectacles that each subject wears in his/her daily life.

During the period of wearing the test spectacles, changes in sleep-wake rhythm will be recorded using an actigraph, and saliva samples will be collected by the research subjects themselves on the day before the start of wearing the spectacles, on the 7th, 14th, 28th and 35th days after the start of wearing, and questionnaires will be administered on the 8th, 15th, 29th and 36th days after the end of wearing the spectacles.

A sleep diary will be filled out daily during the period from Day 1 to Day 36.

10.1.6.1. background information on study subjects

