14.2. Secondary endpoints

(1) Evaluation of circadian rhythm

For the effects of wearing Siam glasses and blue light cut glasses on sleep and diurnal rhythm, objective sleep indices will be analyzed by automatic analysis of actigraph data, followed by visual correction under blind conditions as necessary. Sleep parameters such as time to fall asleep, time to wake up, total time to fall asleep, total sleep time, latency to fall asleep, mid-awake, and sleep efficiency are averaged from Monday to Thursday of each week and compared.

(2) Evaluation of sleepiness, mood, motivation, sleep quality and quantity

For subjective evaluation using a questionnaire, the total scores for I excessive daytime sleepiness, II daytime behavior, III morning symptoms, IV insomnia/rhythm, V holiday sleep rhythm, and VI chronotype were calculated for each week, and the data for each week for the Siam glasses wearer and blue light cut glasses wearer were compared. Statistical analysis was conducted to determine whether there was a significant change in the data with and without blue light cutoff glasses when wearing Siamese glasses or blue light cutoff glasses.

For the NRS, statistical analysis will be conducted to see if there is a significant change in each item for each week when wearing Siamese eyeglasses and when wearing blue light cut eyeglasses, using the corresponding t-tests.

Through these statistical analyses, we will examine whether wearing blue light-cut glasses before bedtime reduces exposure to blue light from smartphones and other devices, prevents the suppression of melatonin release before and after bedtime, and consequently improves sleep quality and prevents delays in the diurnal rhythm.

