14.3. Rationale for setting the target number of cases

Target number of cases: Total 40 cases

(20 cases in the blue light cut glasses pre-fitting group and 20 cases in the Siamese glasses pre-fitting group)

Since there were no previous studies useful for predicting statistical power values in the current study, and since it was difficult to obtain pilot data on a small number of cases due to the nature of the experiment, we were unable to calculate power values for the number of study subjects we considered necessary for the experiment. Tentatively, 40 cases will be used as the sample size for this study, but the results of the statistical analysis will be interpreted with caution to ensure that no type I or type II errors are generated by power analysis or other means.

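### The primary two-way ANOVA and the NRS t-tests leave out the crossover period: precision is lost if the periods differ, and the estimate is biased if the sequences also finish unequal

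*Protocol*

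**What the plan says.** Section 7 describes the trial as "Prospective, randomized, sham-controlled, single-blind, crossover, exploratory study". Section 10.1.5 allocates children to the two wearing orders "in a ratio of 1:1", and section 14.3 plans "20 cases in the blue light cut glasses pre-fitting group and 20 cases in the Siamese glasses pre-fitting group" (the translation renders the sham glasses as Siamese). The first wearing period is Days 1 to 14. For the second, section 10.1.6 says "the switching of the spectacles shall be started on Day 22 and completed on Day 35". Saliva is taken on Days 7 and 14 in the first period and on Days 28 and 35 in the second.

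For the primary endpoint, section 14.1 says melatonin will be "tested by repeated two-way ANOVA for Siamese eyeglass wear and blue light cut eyeglass wear (eyeglass type". The other factor is time, defined as "4 time points at 0, 1, 2, and 3 hours, starting 3 hours before sleep onset", which is the hour within an evening and not the crossover period. The effects named are in the phrase "salivary melatonin concentration was significantly higher for eyeglass type, time trend and interaction". The sentence breaks off there, but by then the model and its terms have been named.

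For the NRS, section 14.2 compares "each item for each week when wearing Siamese eyeglasses and when wearing blue light cut eyeglasses, using the corresponding t-tests". I read these as paired t-tests. No period term appears anywhere in section 14.

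**The concern.** A crossover randomises the order of wearing so that a difference between the two periods can be separated from the effect of the glasses. Melatonin or NRS scores could differ between the periods because of season, the school calendar or growing familiarity with home sampling. The named analyses do not separate this out. Such a shift moves every within-child difference up in one sequence and down by the same amount in the other. The analysis then treats that systematic spread as random error. If the two sequences contribute different numbers of children, the shifts no longer cancel and part of the period effect is reported as a glasses effect.

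This is not detail left to a later analysis plan. The protocol counts and names the factors of its primary model, and period is not among them.

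**Working it through.** **Figure in the plan.** There is none to reproduce. Section 14.3 sets 40 children and says that power could not be calculated. No effect size, SD, period shift or drop-out rate is given.

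**Inputs from the protocol.** Two sequences of 20, two periods, four hourly samples per evening, two-sided 5% (section 14.4).

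**Assumed.** A period shift p of 0 to 1.0, in units of SD_diff, the SD of a child's blue-cut minus sham difference among children in the same sequence.

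**Step 1: reduce the test.** With complete data, the eyeglass-type F test in a two-way repeated-measures ANOVA is the square of the paired t on each child's mean difference d. With a true glasses effect τ, d has mean τ + p in one sequence and τ − p in the other.

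**Step 2: no period term.**
- Bias = p(n1 − n2)/(n1 + n2).
- Variance multiplier = 1 + (p²/SD_diff²) × 4·n1·n2/(N(N − 1)). At 20/20 the last factor is 1600/1560 = 1.026, so the multiplier is about 1 + p²/SD_diff².

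**Step 3: with period.** The estimate is the average of the two sequence means of d. Its SE is √[s²(1/n1 + 1/n2)/4], with s² the pooled within-sequence variance on N − 2 df. The shift p cancels whatever the split.

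**Step 4: balanced, 20/20.** The effect (0.454 SD_diff) is the one with 80% power when there is no shift. Rates are simulated, 10,000 runs per cell.

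| Shift (SD_diff) | SE multiplier | Power without period | Power with period | Type I error without period |
|---|---|---|---|---|
| 0 | 1.00 | 80% | 80% | 4.6% |
| 0.25 | 1.03 | 78% | 80% | 4.6% |
| 0.5 | 1.12 | 72% | 79% | 2.9% |
| 1.0 | 1.42 | 50% | 80% | 0.5% |

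Bias is zero in every row. Simulation error on a 5% rate is √(0.05 × 0.95/10,000) = 0.2 percentage points. The 4.6% at 0.25 SD therefore cannot be told apart from the no-shift row.

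**Step 5: unequal sequences, no period term.**

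| Completers | Bias as share of p | Bias at p = 0.25 / 0.5 / 1.0 (SD_diff) |
|---|---|---|
| 20 v 18 | 2/38 = 5% | 0.013 / 0.026 / 0.053 |
| 20 v 16 | 4/36 = 11% | 0.028 / 0.056 / 0.111 |
| 20 v 15 | 5/35 = 14% | 0.036 / 0.071 / 0.143 |
| 20 v 14 | 6/34 = 18% | 0.044 / 0.088 / 0.176 |

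Its direction depends on the sign of the shift and on which sequence loses more children. With a period term the bias is zero and simulated type I error is 4.5% to 5.5% over the splits tried (20/20, 20/16, 20/14).

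**Step 6: price of the term.** The difference detectable with 80% power at N = 40 moves from 0.4543 SD_diff (39 df) to 0.4546 (38 df).

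**The case against.** The strongest reply is that balanced 1:1 order already protects validity. At 20/20 the estimate is unbiased and the test errs on the conservative side, so only efficiency is lost. The periods start 21 days apart and both start on a Friday, so all four on-treatment sampling days fall on a Thursday and weekday cannot cause a shift. The trial calls itself exploratory and promises cautious interpretation. An analysis plan not shown, or the lost end of the 14.1 sentence, might add period. All of this stands, and it limits the severity. It does not remove the point: the wording at hand is a two-factor model, and balance is not assured at analysis. Section 11.2 allows discontinuation for poor compliance, section 10.1.6.5 uses the Day 15 diary to confirm compliance, when each child has worn only one lens type, and no replacement is described.

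A reader might infer three stronger claims.
- **The omission produces false positives.** The error variance is inflated, not the type I error. Simulated rates were at or below 5% at 20/20. They ran from 1.8% to 4.7% at 20/16 and from 3.9% to 5.1% at 20/14.
- **The damage is known to be large.** That needs a large period shift, and the protocol supports no particular value.
- **A child with one failed saliva tube would be lost.** Section 19.2 leaves missing data to handling criteria set before the data are fixed, so the protocol does not commit to dropping such children.

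**Conclusion.** The point holds as an avoidable loss of efficiency, with a conditional bias. For a two-period crossover, the protocol names a primary model and a set of t-tests that ignore period. A shift of half an SD_diff would cost about 8 percentage points of power at 20/20, and a shift of a full SD_diff about 30. At a quarter of an SD or less with near-equal sequences the cost is small. Bias needs both a shift and unequal completers, and is then 5% to 18% of the shift for the splits shown. These sizes rest on an assumed range of shifts, a constant shift for all children, and complete data for the children analysed. That the documents give no shift or SD limits what can be said about size, not about direction. Severity: should be fixed.

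**What to change.** In section 14.1, add period as a fixed effect. One way is a mixed model with glasses type, hour, glasses type by hour and period as fixed effects and child as a random effect. The random part should keep the child-by-glasses variation that the repeated-measures ANOVA already uses as its error for glasses type, so that the hourly samples of one evening are not treated as independent. In section 14.2, replace the paired t-tests for the NRS with the period-adjusted contrast of Step 3, applied to each item and week.

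A log scale and terms for sequence or for evening within period are optional; the argument here does not require them.

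The cost is a wording change in two sections and about one degree of freedom. No new data are needed.

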14.2. Secondary endpoints

(1) Evaluation of circadian rhythm

For the effects of wearing Siam glasses and blue light cut glasses on sleep and diurnal rhythm, objective sleep indices will be analyzed by automatic analysis of actigraph data, followed by visual correction under blind conditions as necessary. Sleep parameters such as time to fall asleep, time to wake up, total time to fall asleep, total sleep time, latency to fall asleep, mid-awake, and sleep efficiency are averaged from Monday to Thursday of each week and compared.

(2) Evaluation of sleepiness, mood, motivation, sleep quality and quantity

For subjective evaluation using a questionnaire, the total scores for I excessive daytime sleepiness, II daytime behavior, III morning symptoms, IV insomnia/rhythm, V holiday sleep rhythm, and VI chronotype were calculated for each week, and the data for each week for the Siam glasses wearer and blue light cut glasses wearer were compared. Statistical analysis was conducted to determine whether there was a significant change in the data with and without blue light cutoff glasses when wearing Siamese glasses or blue light cutoff glasses.

For the NRS, statistical analysis will be conducted to see if there is a significant change in each item for each week when wearing Siamese eyeglasses and when wearing blue light cut eyeglasses, using the corresponding t-tests.

Through these statistical analyses, we will examine whether wearing blue light-cut glasses before bedtime reduces exposure to blue light from smartphones and other devices, prevents the suppression of melatonin release before and after bedtime, and consequently improves sleep quality and prevents delays in the diurnal rhythm.

14.3. Rationale for setting the target number of cases

Target number of cases: Total 40 cases

(20 cases in the blue light cut glasses pre-fitting group and 20 cases in the Siamese glasses pre-fitting group)

Since there were no previous studies useful for predicting statistical power values in the current study, and since it was difficult to obtain pilot data on a small number of cases due to the nature of the experiment, we were unable to calculate power values for the number of study subjects we considered necessary for the experiment. Tentatively, 40 cases will be used as the sample size for this study, but the results of the statistical analysis will be interpreted with caution to ensure that no type I or type II errors are generated by power analysis or other means.

14.4 Significance Level

The two-tailed test shall be 5%. If multiple comparisons occur, P-values should be corrected as necessary. 15.

15. direct access to source documents

Principal investigators and research institutions will provide all clinical research-related records, including source documents, for direct inspection during investigations by ethics review committees and regulatory authorities related to clinical research.

16. ethical matters

16.1. Compliance with Ethical Principles

This research will be conducted in compliance with the research protocol, the "Ethical Guidelines for Life Sciences and Medical Research Involving Human Subjects" (Ministry of Education, Culture, Sports, Science and Technology, Ministry of Health, Labor and Welfare, and Ministry of Economy, Trade and Industry Notification No. 1, 2021), other relevant laws and regulations, and ethical principles based on the Declaration of Helsinki.

16.2. Ethical Review Committee

This research will be conducted after review and approval by the Ethical Review Committee of the institution to which the principal investigator belongs.

16.3. Anticipated Benefits and Disadvantages to Research Subjects

(1) Benefits to research subjects

 Those who wish to receive the test results (salivary melatonin concentration, circadian rhythm, etc.) will be able to receive feedback.

(2) Acknowledgments to research subjects

 As rewards to research subjects, gift certificates, etc. worth up to 24,000 yen will be offered according to the implementation of the survey, including submission of eyeglass power information, salivary melatonin test, wearing of the ACTIGRAPH, recording of sleep diaries, and responses to questionnaires.

(3) Anticipated disadvantages for research subjects

 The burden of communication fees, such as when using the web conferencing system, will be incurred.

 The subjects will be required to visit an optician to check the power of the eyeglasses they regularly use in their daily lives, which will incur transportation costs and physical restraints.

 Participation in the study requires time and physical restraints for explanation of the study, wearing the equipment, filling out the sleep diary, collecting saliva samples, and answering questionnaires (as a guide, explanation of the study: 1 hour (3 hours for joint explanation), wearing the test equipment: 3 hours/time x 28 times, filling out the sleep diary (e.g., explanation of the test: 5 minutes/time x 36 times, saliva collection: 10 minutes/time x 5 times, and answering questionnaires: 5-10 minutes/time x 4 times).

The test glasses are different from the glasses used regularly in daily life, so there is a possibility that the subjects may feel uncomfortable at the beginning. 16.4.

16.4. Response to health hazards resulting from this study

In the event of any health hazard arising from the implementation of this study, the health insurance of the research subject will be used for the treatment in principle, and appropriate treatment and other necessary measures will be taken so that the subject can receive appropriate treatment.

In this research, all persons involved in this research, including the principal investigator, will be insured by clinical research insurance in preparation for compensation for health damage caused to research subjects.

17. monitoring and auditing

Monitoring and auditing will not be conducted for this research, since it will be conducted in the research subjects' homes and is a minimally invasive research, with the exception of obtaining consent and case registration. 18.

Compliance with and revision of the research protocol

18.1. discontinuation of research

The principal investigator will consider whether or not to continue the research in the following cases

(1) Significant information is obtained concerning the quality, safety, or efficacy of test equipment used in the research

(2) When it is judged that recruitment of research subjects will be difficult and that it will be extremely difficult to achieve the target number of research subjects to be enrolled

(3) When the purpose of the research is achieved before the expected number of research subjects or the research implementation period is reached

(4) When the Ethics Review Committee has given instructions to change the research plan, etc., and it is deemed difficult to accept such instructions. 18.2.

